### Data collection and management

Standardized case report forms will be used for source data during the trial and stored by the investigator in a locked, fireproof place. To ensure privacy of the participants, identifying data will be stored in coded form secured by a password only known to the investigator and principal investigator. Tissue and plasma samples will be stored in coded form and stored in a locked freezer at the surgical laboratory of the principal investigator. Data and human material will be kept for 15 years. Statistical analyses are done by the professional statistician participating in the research staff of the study. (Additional file 2: Appendix 2).

In order to ensure data quality, both the cardiac and liver ultrasound will be carried out by clinical experts and measurements are repeated at least twice per participant per examination. The DXA outcome variables will be evaluated by two specialised nuclear physicians. Anthropometric measurements and microvascular and macrovascular investigations will be performed by a trained laboratory technician; duplicate measurements will be carried out for all of these specific outcomes.

The results of the study will be presented at scientific meetings and published in peer-reviewed medical journals.

### Safety

Serious adverse events and adverse events will be registered in accordance to the standards of Good Clinical Practice. The Dutch Health Care Inspectorate will supervise this clinical trial independently and performs unannounced audits. All early and late operative complications such as wound site infections, slippage of the gastric band, and pouch dilatation of the created gastric pouch will be monitored throughout the entire duration of the trial according to the Clavien-Dindo scoring system [58]. Puberty development will be monitored with growth (body height) and plasma levels of gonadotropins and sex hormones. Nutritional status will be assessed to prevent malnutrition.

The study will be terminated prematurely in case of serious and unexpected complications of surgery, if the complication rate of surgery exceeds the 95% confidence interval of the 10% complication rate considered as normal and in case of serious adverse events that are directly related to the diagnostic procedures performed in this study.

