## Methods

### Study design

We will perform a prospective superiority trial by randomizing severely obese children and adolescents in a 1:1 ratio to receive LAGB on top of the CLI versus CLI treatment alone. The study protocol meets the criteria of the ‘Standard Protocol Items: Recommendations for Interventional Trials’ (SPIRIT) Guidelines (Additional file 1: Appendix 1) [30]. The trial will be carried out at the Maastricht University Medical Centre in the Netherlands. Outcomes will be measured at six, 12, 24 and 36 months from randomisation and will be evaluated after 12 and 36 months.

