To date, bariatric surgery in children and adolescents is prohibited in The Netherlands for all clinical settings except for this trial. Patients from the control group who turn 18 years during the trial period are offered to crossover to the intervention group and receive surgical treatment. If the patient decides for any other type of weight loss surgery after turning 18, this event will be registered yet the patient will still be invited for follow-up visits and be part in the 3-year follow-up analyses. If this trial will provide sufficient data proving that surgical treatment in adolescents is safe and effective, the Dutch Health Care Inspectorate will evaluate and decide whether the remaining patients from the control group can be offered to crossover to the intervention group.

Patients who withdraw from the trial prematurely will receive their regular follow-up from the referring paediatrician. If patients have been operated upon, they will receive their regular surgical follow-up and treatment, but additional trial related investigations will be discontinued.

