### Sample size

The total number of needed study participants was calculated for the primary outcome measure weight loss and is based on the following assumptions: (1) the expected weight loss after 1 and 3 years in the surgery group is 25%; (2) the expected weight change in the control group is 0%, as the patients in the control group have previously been unsuccessfully treated with combined lifestyle interventions; (3) the expected standard deviation is 10% for both groups [55]. To assess a difference in weight loss of 10% or more (7% weight loss is considered to be relevant as it results in a significant improvement in risk and co-morbidity in severely obese adolescents), 44 patients have to be included (α = 0.05, β = 0.10) [56]. Based on previous studies in adults at our institution, we assume that approximately 20% of the patients will not finish the one-year follow-up period, 60 patients need to be included into the study to preserve results on 44 patients treated per protocol. The number of patients necessary to show significant relative excess weight loss or loss of relative excess BMI is smaller. The sample size needed to detect significant and relevant weight loss after surgery compared to conservative treatment will also be sufficient to assess significant differences in insulin resistance and hypertension between both groups. The expected resolution of both insulin resistance or diabetes, and hypertension after surgery is 70–90%, while no effect of continuing life style interventions can be expected [55, 57]. For most of the other variables the currently available information about the expected outcome is not sufficient for a reliable power analysis.

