### Monitoring

To monitor the safety of all patients included in the trial, a Data Safety Monitoring Board (DSMB) will be installed. The board will consist of three independent physicians from the departments of General Surgery and Paediatrics of the Maastricht University Medical Centre. The progress of the trial will be reported to the DSMB after every tenth inclusion in the trial. The report will contain data on all complications of surgery, all adverse events, major protocol deviations and other relevant information per coded participant. The opinion of the DSMB and consequent binding (dis)approval of continuation of the trial will be written down and stored in the trial master file. The medical ethics committee of Maastricht University Medical Centre will be informed about the DSMB opinions.

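### The numerical safety stopping rule cannot be applied reproducibly: a 10% complication rate has no 95% confidence interval until a denominator and a method are given

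*Protocol article*

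**What the plan says.** The Safety section makes early termination mandatory in three situations. The only numerical one is "if the complication rate of surgery exceeds the 95% confidence interval of the 10% complication rate considered as normal". It gives no source or sample size for the 10%, no interval method and no resulting count.

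The same section monitors "All early and late operative complications such as wound site infections, slippage of the gastric band, and pouch dilatation of the created gastric pouch" under the Clavien-Dindo system. The rule itself does not say which grades or what time window enter the rate.

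The Monitoring section sets the reporting schedule: "The progress of the trial will be reported to the DSMB after every tenth inclusion in the trial". On authority it says: "The opinion of the DSMB and consequent binding (dis)approval of continuation of the trial will be written down". It gives no boundary and does not refer back to the rule in the Safety section.

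The number exposed to surgery follows from two other places. Study design describes "randomizing severely obese children and adolescents in a 1:1 ratio to receive LAGB on top of the CLI versus CLI treatment alone", and Sample size states that "60 patients need to be included into the study to preserve results on 44 patients treated per protocol".

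**The concern.** A confidence interval describes the uncertainty of an estimate from a sample of known size. A reference rate of 10% with no sample behind it has none. At least three readings fit the sentence:

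- **Reading 1.** An interval is drawn around 10% using the number operated so far, and the observed rate is compared with its upper limit.
- **Reading 2.** An exact binomial boundary at 10% is used. This gives the same counts as requiring the lower exact 95% limit of the observed rate to lie above 10%.
- **Reading 3.** The 10% comes from an earlier series, and that series' fixed interval is the yardstick.

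If these readings gave the same counts, the wording would be harmless. If they do not, a DSMB with a binding vote on a trial in 14- to 16-year-olds could look at one set of data and defensibly either stop or continue. The readings matter most at the early reports, when most patients have yet to be allocated.

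**Working it through.** **The plan's own figure.** The article prints no boundary count or upper limit, so there is none to reproduce.

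**Inputs.** Total 60 (Sample size), allocation 1:1 (Study design) and a report after every tenth inclusion (Monitoring). This gives 60/10 = 6 reports, with about 10/2 = 5 more patients allocated to surgery each time: 5, 10, 15, 20, 25, 30. The reference rate is 10% (Safety).

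**Assumptions.** Every allocated patient has been operated on and is evaluable at the report, the unit is patients with at least one counted complication, and patients are independent. True rates of 20% and 30% are illustrative.

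**Reading 1, Wald interval at the current n.** Upper limit = 0.10 + 1.96 × √(0.10 × 0.90 / n). For n = 5 this is 0.10 + 1.96 × √0.018 = 0.363, so 2/5 = 0.40 exceeds it. For n = 30 it is 0.207, so 7/30 = 0.233 exceeds it.

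**Reading 2, exact binomial.** The stopping count is the smallest x with P(X ≥ x | n, 0.10) < 0.025. For n = 5, P(X ≥ 2) = 0.0815 and P(X ≥ 3) = 0.0086, so the count is 3. For n = 30, P(X ≥ 7) = 0.0258 and P(X ≥ 8) = 0.0078, so the count is 8. Requiring the Clopper-Pearson lower 95% limit to exceed 10% gives the same counts: at 7/30 that limit is 9.93%, and at 8/30 it is 12.28%.

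**Reading 3, fixed interval of a historical series.** The Clopper-Pearson upper limit for an observed 10% is 17.6% with 100 patients, 15.0% with 200 and 12.0% with 1000 (all sizes assumed). One of five is 20%, which exceeds all three.

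| Operated | 5 | 10 | 15 | 20 | 25 | 30 |
|---|---|---|---|---|---|---|
| Wald upper limit around 10% | 36.3% | 28.6% | 25.2% | 23.1% | 21.8% | 20.7% |
| Stop at, Wald | 2 | 3 | 4 | 5 | 6 | 7 |
| Stop at, exact binomial | 3 | 4 | 5 | 6 | 7 | 8 |
| Stop at, series of 100 | 1 | 2 | 3 | 4 | 5 | 6 |
| Stop at, series of 1000 | 1 | 2 | 2 | 3 | 4 | 4 |

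**Chance of stopping at any of the six reports.** This was calculated exactly by adding a Binomial(5, p) increment at each report and removing the paths that have already crossed the boundary.

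| True rate | 10% | 20% | 30% |
|---|---|---|---|
| Wald | 14.6% | 59% | 91% |
| Exact binomial | 3.2% | 35% | 79% |
| Series of 100 | 49% | 86% | 98% |
| Series of 1000 | 63% | 94% | 99.6% |

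Under the historical-series reading, the first report alone stops a trial with a true 10% rate with probability 1 − 0.9⁵ = 41%.

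**A concrete case.** Two patients with a complication among the first five operated (40%) stop the trial under the Wald and historical-series readings. They do not under the exact reading, which needs three.

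**The case against.** The strongest reply has four parts.

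1. *An article condenses.* Boundary tables and the handling of repeated looks usually sit in the full protocol or a DSMB charter, which are not shown. That stands for the operating characteristics, and their absence alone would be no finding. It does not rescue the sentence, because the article chose to state a mandatory threshold in terms that have no value as written.

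2. *The readings based on the trial's own numbers are close.* That is true in counts: Wald and exact binomial differ by one patient at every report, 7 against 8 at the end. That one patient still takes the chance of stopping at the reference rate from 3.2% to 14.6%. The widest spread needs the historical-series reading, whose size is assumed here.

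3. *The look schedule is a reconstruction.* The Monitoring section counts inclusions, and surgery follows within six weeks of randomisation, so fewer may have been operated at each report. The Safety section also does not tie its rule to those reports. This stands. The percentages illustrate the ambiguity and are not properties of a schedule the plan has fixed.

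4. *Protection does not rest on this sentence alone.* There are two other termination triggers, supervision by the Health Care Inspectorate, and a DSMB that sees all complications. This stands and limits the consequence.

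A reader might also infer that 30 operated patients can never show safety against 10%, and that the plan promises to do so. The documents do not support this. The Study outline wording is conditional ("If this trial will provide sufficient data proving that surgical treatment in adolescents is safe and effective") and leaves the judgement to the Inspectorate. The 10% is used only as a stopping reference, and safety is nowhere defined as excluding it. Nor is it arithmetically impossible: with 0/30 the one-sided 95% upper limit is 1 − 0.05^(1/30) = 9.5%. The number operated may also exceed 30, since "Patients from the control group who turn 18 years during the trial period are offered to crossover to the intervention group and receive surgical treatment".

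**Conclusion.** The point holds for the stopping rule. It is a stated decision threshold that is badly fixed, because without a denominator and a method it yields no count. Depending on the reading, the first report stops at 1, 2 or 3 of 5. The chance of ever stopping at a true 10% rate runs from 3.2% to 14.6% for the two trial-based readings tabulated, and reaches 49–63% for an assumed historical series of 100 to 1000. At a true 20% it runs from 35% to 94%. These figures rest on the assumed numbers operated at each report and on one binary outcome per patient. The conclusion that the rule is ambiguous does not depend on them.

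Nothing is concluded about whether the trial can establish safety. At most, the complication rate will be imprecise: the exact two-sided 95% interval is 0–11.6% for 0/30 and 2.1–26.5% for 3/30.

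**What to change.** Keep the sponsor's 10% reference and replace the sentence in the Safety section with a table of cumulative counts by number of patients operated.

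- Derive the table from one named method. One example is that the lower limit of the exact Clopper-Pearson 95% interval for the observed rate exceeds 10%; under the assumed schedule this gives the exact binomial row above.
- Index it by patients actually operated rather than inclusions, so that it still applies when surgery lags behind randomisation.
- Print the overall stopping probabilities at true rates of 10%, 20% and 30% beside it, so the DSMB can see the effect of repeated looks and the sponsor can judge whether they are acceptable.
- Refer to the table from the Monitoring section, so that the rule and the reports to the DSMB are linked.
- State whether patients or events are counted. The sponsor's clinicians decide which complications, grades and time window enter the rate.
- Report the final complication rate with its exact 95% interval.

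The cost is about one page in the protocol or DSMB charter. It needs no extra patients, visits or data.

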### Monitoring

To monitor the safety of all patients included in the trial, a Data Safety Monitoring Board (DSMB) will be installed. The board will consist of three independent physicians from the departments of General Surgery and Paediatrics of the Maastricht University Medical Centre. The progress of the trial will be reported to the DSMB after every tenth inclusion in the trial. The report will contain data on all complications of surgery, all adverse events, major protocol deviations and other relevant information per coded participant. The opinion of the DSMB and consequent binding (dis)approval of continuation of the trial will be written down and stored in the trial master file. The medical ethics committee of Maastricht University Medical Centre will be informed about the DSMB opinions.

## Discussion

The BASIC trial is designed to provide high-quality data on the safety and efficacy of LAGB treatment in severely obese children and adolescents. Lack of available long-term data on safety and efficacy of bariatric surgery in youngsters advocates an extremely cautious approach and intensive monitoring of growth and development in these specific patients. Nevertheless, severe obesity has already proven to impair children and adolescents in their pubertal and psychosocial development and significantly increases risks for development of cardiovascular diseases amongst others [2–6]. The BASIC trial will provide tertiary and multidisciplinary care for its participants: comprehensive health examinations will be carried out throughout the trial and results will be discussed in a multidisciplinary setting to guarantee optimal care for this vulnerable population. This is the first randomized controlled trial investigating bariatric surgery as a complementary treatment in adolescents with failed combined lifestyle interventions. Outcome measurement will focus primarily on percentages of total weight loss and excess weight loss, yet a comprehensive set of secondary outcome measures will be provided as well.

A potential limitation of this study includes the choice of LAGB treatment over other bariatric procedures as investigational intervention. Laparoscopic adjustable gastric banding is a restrictive bariatric procedure that can be reversed easily and enables weight loss without altering absorptive processes. The reversibility of the LAGB procedure formed an important argument in this study design of this experimental trial, since the study population is very young and patients might want to make use of possible new and innovative treatment options in the future. Other bariatric procedures have proven to be more effective in terms of excess weight loss and improvement of comorbidity in adults, though these results do not necessarily apply to children and adolescents in the same extent [21, 25].

Secondly, this study may be at risk for relative high loss-to-follow up rates throughout the study period. Because of the comprehensive attempts to lose weight (without intended effect) prior to enrolment in this study, patients may have developed a certain attitude towards healthcare systems and providers negatively affecting their compliance and their stamina. Allocation to the control group might amplify these developments, resulting in high risks for getting loss-to-follow up. The coordinating investigator of the BASIC trial will be aware of these risks and attempt to keep the patients involved with their own health status and potential beneficial treatment methods. Patients and their parents will be informed of the results of their annual comprehensive medical examination and will be involved in the possible adjustments that have to be made to the combined lifestyle interventions and/or gastric band care if applicable.

In summary, this randomized controlled trial will provide important information on the safety and efficacy of LAGB surgery in severely obese adolescents with unsuccessful CLI. The unique control group will provide a necessary framework of data regarding physiological changes throughout adolescence and pathophysiological effects of persistent childhood severe obesity. The results of this study may steer the international opinion regarding treatment options of severely obese adolescents who still have most of their lives ahead of them.

## Abbreviations

ASA class: American Society of Anesthesiologists physical status classification
BMI: Body mass index
chEDE-Q: Child version of eating disorders examination questionnaire
CLI: Combined lifestyle interventions
DSMB: Data Safety Monitoring Board
DSM-IV: Diagnostic and Statistic Manual of Mental disorders 4th edition
DSM-V: Diagnostic and Statistic Manual of Mental Disorders 5th edition
DXA: Dual energy X-ray absorptiometry
HRQOL: Health related quality of life
IGT: Iowa Gambling Test
LAGB: Laparoscopic adjustable gastric banding
LRYGB: Laparoscopic Roux-and-Y gastric bypass
LSG: Laparoscopic sleeve gastrectomy
mmHg: Millimeters of mercury
mmol/L: Millimoles per liter
OSA: Obstructive sleep apnea
PedsQL: Pediatric Quality of Life inventory
PFS: Power of Food Scale
SPIRIT: Standard Protocol Items Recommendations for Interventional Trials
SST: Stop Signal Test
T2DM: Type two diabetes mellitus
TBW: Total body water
TFEQ: Three Factor Eating Questionnaire
WLT: Wanting and Liking Test
